### Recruitment method and study procedures

The study team will contact eligible young people (and/or an adult with parental responsibility for young people aged 13–15 years old) by telephone, text or email to invite the young person to take part. They will be sent a unique link to the study website which will host the participant information and online consent and assent forms as well as being offered the option of a face-to-face or virtual meeting if needed. Young people aged 16–25 years old who want to take part, will be asked to confirm their consent via an online form. This will include separate consent for the following types of data collection: questionnaires, EHRs, social media and smartphone data; choosing not to consent to the latter three will not preclude participation. For young people aged 13–15 years old, an adult with parental responsibility will first be asked to confirm their consent via an online form, following which the young person will be asked to confirm their assent. A maximum of three contact attempts will be made to non-responders. The flow of participants through the study will be documented in a flowchart (see figure 1 - Participant flowchart).

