### Sample size calculation

In a recent national community survey, the reported annual age-sex incidence of self-harm for young people aged 16–18 years old was 36.4% (95% CI 22.4 to 52.2) for men and 43.5% (95% CI 35.5 to 51.7) for women.^3^ Based on uptake of SLaM C4C patient research participation register, we estimate that if 600 young people consent to take part, 480 will be followed up during a 6-month period, resulting in at least 150 with an episode of self-harm. Using the most conservative estimates, if approximately 22.5% of those who do not display characteristic problematic patterns of social media usage (or smartphone usage) have an episode of self-harm and this increases to 35% in those identified with problematic usage in the previous week, we expect 86% power to detect a 12.5% increase in self-harm at 5% significance, assuming 480 young people are followed up.

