#### Primary analysis

Patterns of social media and smartphone use will be identified and categorised into specific problematic exposure groups. This will be defined using a mixed methods analysis comparing social media and smartphone data in the 7 days leading up to a self-harm episode. Individuals who do not experience an episode of self-harm will be randomly matched with four cases, and the same relative date and time of exposure will be randomly matched.

Social media and smartphone use will be compared between self-harm cases and non-cases, including social media platform of use, duration of use, time of use and absence of engagement (reduced level of posting but passive presence online). For example, night-time use compared with similar use during the day will be compared by self-harm status.

A binary generalised linear model with a log link will be fitted to derive the relative risk of a prospective self-harm episode in relation to a characteristic pattern of social media and smartphone use in the 7 days prior to the episode. Known social and physical determinants of health associated with self-harm will be included to adjust for baseline effects. Missing data will be explored for patterns of missingness. Secondary analyses will explore potential mediating effects of anxiety, depression, sleep disturbance, loneliness and bullying.

The primary analysis population under investigation will include all participants with a post-baseline assessment of self-harm.

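### The 86% power and the primary population assume a classified 7-day exposure for all 480 followed up, although smartphone and social media data are optional

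*Protocol article*

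**What the plan says.** **Consent.** Under Recruitment method and study procedures, consent is taken separately for questionnaires, health records, social media data and smartphone data, and "choosing not to consent to the latter three will not preclude participation". That sentence sits with the description of consent at ages 16–25; Ethics and safety considerations extends the choice of what to share to participants generally. People who decline smartphone metadata, or who do not use the app for another reason, stay in the study through an online survey.

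**Primary population and model.** Under Primary analysis: "The primary analysis population under investigation will include all participants with a post-baseline assessment of self-harm". The same section fits a log-link binary model for the relative risk of self-harm according to the pattern of use in the 7 days before the episode. Non-cases receive a matched date and time of exposure.

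**Power.** Under Sample size calculation, "if 600 young people consent to take part, 480 will be followed up during a 6-month period". The contrast is that "approximately 22.5% of those who do not display characteristic problematic patterns of social media usage (or smartphone usage) have an episode of self-harm" and that "this increases to 35% in those identified with problematic usage in the previous week". The result is that "we expect 86% power to detect a 12.5% increase in self-harm at 5% significance, assuming 480 young people are followed up".

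**Other usage measures.** Exposures also lists self-reported use. Table 2 places self-reported use at baseline and month 6, and the SAS-SV at baseline, month 4 and month 6.

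**Acknowledgement.** The strengths and limitations box concedes that flexible sharing raises the risk of missing and inconsistent data. Primary analysis says patterns of missingness will be explored.

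**The concern.** Three statements do not fit together. Exposure data are optional, the primary model cannot be fitted without them, and both the population and the power are stated as if everyone followed up had them.

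The self-report measures do not close the gap. They record average daily use or a problematic-use score at a few fixed visits, so they cannot be placed in the particular week before an episode or in a non-case's matched week. Only app metadata or uploaded platform data can be dated in that way.

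Two things are at stake. The first is the headline power, which belongs to a number analysed that is reached only if every followed-up participant has usable exposure data. The second is the meaning of the primary result. If the model is fitted only where exposure exists, the population analysed is not the one stated, and it has been selected on willingness to share.

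**Working it through.** **Inputs.** From Sample size calculation: self-harm risk 22.5% without and 35% with a problematic pattern; 5% significance; 480 followed up out of 600. Not stated there, and therefore assumed: a two-sided test, equal exposed and unexposed groups, and the fraction *f* of the 480 with exposure data covering the index or matched window.

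**Formula.** Two proportions, normal approximation with pooled variance under the null, *n* per group:

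power = Φ{ [d√n − 1.96·√(2·p̄(1−p̄))] / √(p1(1−p1) + p2(1−p2)) }

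- d = 0.35 − 0.225 = 0.125
- p̄ = (0.225 + 0.35)/2 = 0.2875, so √(2 × 0.2875 × 0.7125) = 0.6401
- √(0.225 × 0.775 + 0.35 × 0.65) = √0.401875 = 0.6339

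**Step 1: reproduce the stated power.** With n = 240 per group, √n = 15.492. The numerator is 0.125 × 15.492 − 1.96 × 0.6401 = 1.9365 − 1.2545 = 0.6820. Dividing by 0.6339 gives 1.076, and Φ(1.076) = 0.859. The stated 86% is therefore matched with 240 v 240, two-sided and without continuity correction. The alternatives do not match: one-sided gives 91.8% and continuity-corrected gives 83.5%. All 480 must carry a classified exposure.

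**Step 2: identify what has been deducted.** The only reduction is 600 to 480, which is 480/600 = 80% followed up. Nothing is taken off for participants without exposure data.

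**Step 3: let only a fraction *f* of the 480 have exposure data.** Same formula, equal split:

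| f (assumed) | Number with exposure data | Power |
|---|---|---|
| 100% | 480 | 85.9% |
| 90% | 432 | 82.1% |
| 80% | 384 | 77.4% |
| 75% | 360 | 74.7% |
| 70% | 336 | 71.8% |
| 60% | 288 | 65.1% |
| 50% | 240 | 57.2% |

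**Step 4: threshold.** Solving for 80% power gives 205 per group, 410 in total; 410/480 = 85%.

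**Step 5: sensitivity to the equal split.** With all 480 retained, power is 80.3% if 30% are exposed and 70.2% if 20% are. The table therefore shows the more favourable end for each *f*.

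**Step 6: could enrolment absorb the loss?** Keeping 480 with exposure data needs 480/(0.8 × f) enrolled. That is 667 at f = 90% and 750 at f = 80%, both above the planned maximum of 600.

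**The case against.** The strongest reply is that the loss may be small. The article gives no sharing rate, and at 90% coverage power is still 82%. Declining one source does not remove a person from the other, since the sample size section words the exposure as social media or smartphone usage. Uploads also reach back to the creation of the account, so a month-6 upload can fill a window missed at month 3. All of this stands. The loss in each analysis is confined to people without coverage in the source being analysed, and its size is unknown.

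A second reply is that the risk is disclosed and that detailed handling belongs in the analysis plan. That is fair for the handling of missing exposure. It does not answer the point, because the article itself fixes a population and a power figure, and the disclosure changes neither.

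Two stronger readings are tempting but not supported:

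- A reader might infer that non-sharers would be classed as exposed through the disengagement pattern. The article defines that pattern as "absence of engagement (reduced level of posting but passive presence online"), which requires evidence of presence and a level to fall from. A non-sharer supplies neither. Consent is also recorded by data type, and nothing says that missing records will be coded as zero use.
- A reader might infer that 480 can never be reached. With the sharing rate unknown, the documents show only that 480 requires usable exposure data from every followed-up participant.

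Finally, restricting to sharers has its own weakness, because willingness to share may be related to self-harm. This is a fair caution, and the change proposed has to allow for it.

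**Conclusion.** The point holds as a mismatch between the stated population and power on one side and the primary model on the other. The 86% is not an arithmetic error. It is conditional on complete exposure classification, which the design does not require of participants.

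The mismatch follows from the text. Its size does not, and depends on three assumptions: the fraction with usable data in the source analysed, the equal split, and the stated 22.5% and 35% risks. Over an assumed range of 90% down to 50%, power runs from 82% to 57%, and it drops below 80% under about 410 participants with exposure data. Smartphone and social media coverage may differ, so one figure cannot describe both analyses.

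**What to change.** 1. In Primary analysis, state that the model for each source (smartphone, social media) is fitted in participants who have a post-baseline self-harm assessment and data from that source covering the index 7-day window or, for non-cases, the matched one.
2. State that the absence of a record is treated as missing, not as zero use.
3. In Sample size calculation, replace the single 86% with a figure for each source at the sharing rate observed to date, and state the assumed exposed/unexposed split.
4. Compare sharers with non-sharers on baseline characteristics and on self-harm, since the restriction may select on willingness to share. A prespecified missing-exposure method can serve as a sensitivity analysis.

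The cost is wording, a less favourable stated power and a little extra analysis. No further participants or procedures are needed.

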**Figure 1 F1:**
[figure not shown]
Participant flowchart.

Participants will then instal the study software application on their smartphone device and complete the baseline questionnaires. The study software application has been designed to continuously extract smartphone metadata and to deliver the questionnaires for the follow-up period (up to 6 months, reduced from 12 months following an initial pilot phase). Tables 2 and 3 outline data collection measures over the 6-month follow-up period related to primary and secondary objectives and other measurements. Participants who choose not to provide smartphone metadata (or use the study software application for any other reason) will be provided with a unique link to an online survey platform—Qualtrics (https://www.qualtrics.com)—to complete the questionnaires according to the same schedule. Participants will receive a reminder (an automated push notification and/or a prescheduled standardised text message and/or email) on the day a questionnaire is due, followed by a second reminder 7 days later if incomplete. The final set of questionnaires may also be sent via post. Participants who consent to provide their social media data will be contacted at baseline, months 3 and 6 to ask them to upload data. Participants will be given detailed guidance on how to request their data from the platforms and upload it to the study website via a unique link. Participants will receive a £10 voucher as a thank you for enrolling in the study, followed by £5 per month of continued participation and an additional £10 voucher for uploading their social media data at month 6.

**Table 2 T2:** Outline of data collection measures over the 6-month follow-up period related to primary objectives

Measure	Description	Data collected at:						
		Baseline	Month 1	Month 2	Month 3	Month 4	Month 5	Month 6
Socio-demographic questionnaire	Including age, gender, ethnicity, education and/or employment status, smoking, alcohol consumption and drug use.	X						
Child and Adolescent Self-harm in Europe (CASE) study criteria^48^	Occurrence and characteristics of historical and current (ie, in the last month) self-harm events will be collected using an adapted self-report version of the two-item CASE study criteria.^48^	X	X	X	X	X	X	X
Self-reported social media use	Including which social media platforms are used, types of activity (eg, to share something, or to comment on a post) and average duration of daily usage.	X						X
Self-reported smartphone use	Including most frequently used apps, average duration of daily usage, and night-time access to a smartphone.	X						X
Smartphone Addiction Scale - Short Version (SAS-SV)^49^	Smartphone addiction will also be measured using the 10-item SAS-SV.^ 49 ^ Scores range between 10 and 60, with 31 and 33 representing a cut-off for smartphone addiction in adolescent boys and girls, respectively. The SAS-SV is a widely used and validated instrument which operationalises problematic smartphone usage.^50^	X				X		X
Social media data upload	Retrospective (ie, since the account was created) and prospective social media data will be uploaded by participants from their accounts on Facebook, Instagram, Snapchat, TikTok, Twitter and YouTube, including duration of usage (hours/min per day), timing of usage (diurnal/nocturnal posting), frequency of usage (visits to platforms per day), type of use and textual and imagery data.	X			X			X
Smartphone metadata extraction	Smartphone metadata will be extracted continuously for the duration of follow-up using the study software application, including intensity of usage by time of day, frequency and duration of incoming and outgoing telephone calls, frequency of incoming and outgoing text messages and length of time spent on software applications. For participants with Android phones, permissions will be set to enable the Android App Usage API to track daily statistics listed above. For iOS, low level system logs will be used to retrieve similar information as listed above, where iOS allows.	X	X	X	X	X	X	X
Electronic health records data extraction	Clinician recorded self-harm events, using a similar approach to Polling *et al,* 51 and other relevant clinical variables will be extracted from structured and free-text fields in EHR using the CRIS system. For participants who provide social media data, data will be extracted from the date of the first interaction on social media (or the date of the 13th birthday, whichever is later) to the end of the follow-up. For participants who do not provide social media data, data will be extracted from the date of the baseline assessment.	X						X

CRIS, Clinical Research Interactive Search; EHR, electronic health record.

**Table 3 T3:** Outline of data collection measures over the 6-month follow-up period related to secondary objectives and other measurements

Measure	Description	Data collected at:						
		Baseline	Month 1	Month 2	Month 3	Month 4	Month 5	Month 6
Generalised Anxiety Disorder (GAD-7)^52^	Symptoms of anxiety will be measured using the 7-item GAD-7 scale.^52^ Scores range between 0 and 21, with scores of 5, 10 and 15 representing the cut-off points for mild, moderate and severe anxiety, respectively.	X				X		X
Patient Health Questionnaire (PHQ-9)^53^	Symptoms of depression will be measured using the 9-item PHQ-9.^53^ Scores range between 0 and 27, with scores of 5, 10, 15 and 20 representing the cut-off points for mild, moderate, moderately severe and severe depression, respectively.	X	X		X		X	X
PROMIS Sleep Disturbance Short Form / Paediatric Sleep Disturbance Short Form^54 55^	Symptoms of sleep disturbance will be measured using the 4-item Patient-Reported Outcomes Measurement Information System (PROMIS) Sleep Disturbance Short Form V.1.0 4a (for >18 year olds)^54^ or the Paediatric Sleep Disturbance Short Form V.1.0 4 a (for 5–17 year olds).^55^ Raw scores range between 4 and 16, and these are standardised using a T-score metric, with T-scores of 55, 60 and 70 representing the cut-off points for mild, moderate and severe sleep disturbance, respectively.	X		X		X		X
Three-Item Loneliness Scale^56^	Feelings of loneliness will be measured using the 3-item Loneliness Scale.^56^ Scores range between 3 and 9, with higher scores indicative of greater feelings of loneliness.	X			X			X
Eight-item bullying checklist^57^	Experiences of bullying victimisation will be measured using the 8-item bullying checklist^57^ derived from the Revised Olweus Bully/Victim Questionnaire.^58^ Eight statements are rated using a 5-point response scale, with ‘2 or 3 times a month’ representing a cut-off point for regular bullying victimisation.	X		X			X	X
Exposure to COVID-19 questionnaire*	Self-reported exposure to COVID-19 will be measured using two items from the Wave 2 survey of the Millennium Cohort Study.^59^	X						X

*Indicates that these are other measurements, not related to the primary and secondary objectives.

### Outcomes, exposures and other measurements

#### Primary outcome

Participant and clinician recorded self-harm events.

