**Methods and analysis:**

To study the mechanisms by which social media and smartphone use underpin self-harm in a clinical sample of young people, the Social media, Smartphone use and Self-harm in Young People (3S-YP) study uses a prospective, observational study design. Up to 600 young people aged 13–25 years old from secondary mental health services will be recruited and followed for up to 6 months. Primary analysis will compare real-world data in the 7 days leading up to a participant or clinician recorded self-harm episode, to categorise patterns of problematic usage. Secondary analyses will explore potential mediating effects of anxiety, depression, sleep disturbance, loneliness and bullying.

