## Introduction

Self-harm is characterised as any behaviour where an individual causes damage or injury to their body in response to distress. Traditionally, research has focused more on severe cases of self-harm, namely cutting or self-poisoning, rather than a broader spectrum of behaviour, including burning, scratching or hitting oneself. Self-harm in young people is a significant public health concern, with findings indicating that more than 15% of the young people report engaging in self-harm in the community, coupled with high rates of repetition and elevated risk of suicide.^1–3^ Prevalence figures are likely to underestimate the true scale of the problem, given young people are often reluctant to disclose and seek professional help owing to fear of stigma.^4^ Furthermore, epidemiological studies tend to rely on hospital presentations and only reflect those cases of self-harm that are brought to medical attention.^5^ Whereas community and school-based studies collect self-reported retrospective data. Therefore, while capturing a wider range of self-harm behaviours, they lack information about the specific timing and nature of non-help seeking self-harm.

Reasons for self-harm are complex and multifaceted, however there has been an increasing speculation about the potential negative impacts of social media and smartphone use on youth mental health.^6^ Young people are the most frequent users of social media and smartphones, with 91% of 12–15 year olds using social media and 98% of 13-year olds owning a smartphone in the UK.^7^ Over the last decade, social media and smartphones have altered how young people spend their time and interact socially with peers.^8^ This coincides with a sharp increase in the levels of self-harm, particularly among adolescent women.^9^ Given the widespread use of social media and smartphones, understanding the implications for youth mental health is of paramount importance.

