### Data analysis plan

#### Descriptive analysis

Individuals will be grouped into those that have had an episode of self-harm, and those that have not. Frequency distributions for different types of self-harm will be summarised, and individuals with multiple, versus a single episode of self-harm will be compared. Baseline sociodemographic and clinical descriptors will be presented for those that self-harm and those that do not. Patterns of social media and smartphone use will be explored using a mixed methods analysis and presented as a descriptive analysis.

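### Case status in the primary analysis depends partly on optional consent to health-record access, because an episode from either source counts and the analysis ignores which source was available

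*Protocol article*

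**What the plan says.** The Primary outcome section of the protocol article gives one item: "Participant and clinician recorded self-harm events". The abstract words the qualifying event as a "participant or clinician recorded self-harm episode", so one source suffices.

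The two sources are collected differently. Self-report comes from the adapted CASE items at baseline and every month (Table 2: "Occurrence and characteristics of historical and current (ie, in the last month) self-harm events will be collected"). Clinician events come from extraction of the electronic health record (also Table 2).

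Under Recruitment method and study procedures, the article says of consent: "This will include separate consent for the following types of data collection: questionnaires, EHRs, social media and smartphone data". It adds that "choosing not to consent to the latter three will not preclude participation". Questionnaires are thus the only component that every participant takes on; record access is optional.

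The Descriptive analysis section splits participants into those with and without an episode. The Primary analysis section matches non-cases at random and fits a log-link model for the relative risk. It sets the population as follows: "The primary analysis population under investigation will include all participants with a post-baseline assessment of self-harm". It does not say which source must supply that assessment.

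**The concern.** Two people with the same self-harm history can receive different labels. If the only trace of an episode is a clinician's entry, the participant who allowed record access is a case. The one who refused is a non-case and can be drawn as a comparison subject. The planned exploration of missingness would not correct this, because the second participant does not appear as missing. They appear as someone who did not self-harm.

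What is at stake is the comparability of outcome ascertainment between exposed and unexposed. Both the exposure data and the record data depend on what a participant chooses to share, so a link between usage pattern and record consent is possible, although nothing in the article shows one. If it exists, part of the estimated relative risk reflects who could be observed.

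**Working it through.** **The plan's own figure.** The sample size section states 86% power for 22.5% versus 35% with 480 followed up at 5%. With 240 per group, two-sided:
- Pooled rate 0.2875; null SE = √(0.2875 × 0.7125 × 2/240) = 0.0413; alternative SE = √[(0.225 × 0.775 + 0.35 × 0.65)/240] = 0.0409.
- z = (0.125 − 1.96 × 0.0413)/0.0409 ≈ 1.08, which gives power of 85.9%. The figure is reproduced. The planned relative risk is 0.35/0.225 = 1.56.

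**Assumptions (none is in the documents).** Self-report captures a share s of true cases (0.6 to 0.9). Records independently capture a share e (0.2 to 0.4). A share c of a group gives record consent. Capture does not otherwise differ by exposure.

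**Effect on one person.** Capture is s without record consent and 1 − (1 − s)(1 − e) with it. The ratio of the two is:
- s = 0.9, e = 0.2: 0.92/0.90 = 1.02
- s = 0.8, e = 0.4: 0.88/0.80 = 1.10
- s = 0.6, e = 0.4: 0.76/0.60 = 1.27

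**Effect on the relative risk.** Group capture is s + c(1 − s)e. The observed relative risk is the true one times capture in exposed over capture in unexposed.

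| s, e | capture at c = 0.9 | capture at c = 0.5 | factor, exposed 90% vs unexposed 50% | 1.56 becomes | factor if reversed | 1.56 becomes |
|---|---|---|---|---|---|---|
| 0.9, 0.2 | 0.918 | 0.910 | 1.01 | 1.57 | 0.99 | 1.54 |
| 0.8, 0.4 | 0.872 | 0.840 | 1.04 | 1.62 | 0.96 | 1.50 |
| 0.6, 0.4 | 0.744 | 0.680 | 1.09 | 1.70 | 0.91 | 1.42 |

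With equal consent in both groups the factor is exactly 1. The impossible-to-exceed contrast of 100% versus 0% gives 1.02, 1.10 and 1.27.

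**Power when consent is unrelated to exposure.** If 22.5% and 35% are true rates, then with s = 0.8 and e = 0.4 power is 79% at full record consent, 77% at 50% and 74% at none. Lack of record consent thus accounts for up to 5 points in this scenario.

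**Entry on records alone.** The population sentence does not exclude a participant who returned no follow-up questionnaire and whose record search found nothing. On that reading, let nr be the share not returning questionnaires. Capture in a group is [(1 − nr)·R + nr·c·e] / [(1 − nr) + nr·c], where R is capture among those who return. With s = 0.8, e = 0.3, c = 0.75:
- R = 0.75 × 0.86 + 0.25 × 0.80 = 0.845.
- nr = 0.30: (0.5915 + 0.0675)/0.925 = 0.712. nr = 0.10: (0.7605 + 0.0225)/0.975 = 0.803.
- More non-return in exposed: factor 0.712/0.803 = 0.89, so 1.56 becomes 1.38. More non-return in unexposed: factor 1.13, so 1.56 becomes 1.75.

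The direction therefore follows the assumption, and equal non-return gives no bias.

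**Why adjustment works.** Under these assumptions record consent multiplies the labelled risk by a constant (1.02 to 1.27). A main effect for consent in a log-link model absorbs such a multiplier. With self-report only, capture is s in both groups and the factor is 1.

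**The case against.** The best case against is that the effect is modest and conditional. It needs record consent to be related to the usage pattern, and no passage says that it is. Recruits from the Consent for Contact register have already allowed access to their records for recruitment, so record consent may be high throughout and the contrast small. The article also admits, among its strengths and limitations, that flexible data sharing may harm validity, and it plans to look at missingness. All this stands and limits the size. It does not remove the unequal labelling, which the article's own outcome, consent and population wording produces. The separate-consent text follows the sentence on 16-25 year olds, but the ethics section says generally that participants choose what to share.

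Four stronger readings are tempting and not supported:
- **The bias runs towards 1.** A reader might link the low-engagement pattern to unreturned questionnaires. The article describes that pattern as posting less while still present online, so the link is conjecture.
- **The 120 participants not expected to be followed up enter as non-cases.** The article does not say that an empty record search is an assessment of self-harm. The sample size counts only the 480, and each person also needs exposure data for a 7-day window.
- **An episode found in both sources is counted twice.** Nothing says that records are summed. The comparison is stated by episode: "individuals with multiple, versus a single episode of self-harm will be compared".
- **The model's covariates overlook source availability.** The article names only a class of determinants, so what the list omits cannot be known.

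**Conclusion.** The point holds in a limited form. As written, a clinician-recorded episode that was not self-reported makes a case of a participant with record consent and an eligible non-case of one without it. Episodes that are self-reported are unaffected.

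The relative risk is biased only if record consent or questionnaire return is related to the usage pattern. For consent, the spurious relative risk is about 1.01 to 1.09 at 90% versus 50%, the inverse if the contrast is reversed, and none if consent is unrelated to exposure. These sizes rest on assumed and independent capture rates and on risks in the full cohort; they do not carry over exactly to the planned matched comparison. The route through questionnaire non-return depends on a reading that the article leaves open, and its direction cannot be determined from the documents.

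**What to change.** 1. Draw matched non-cases from the same record-consent group as the case, or include record consent as a covariate in the log-link model.
2. Repeat the primary relative risk with self-reported CASE events only, the one source open to every participant.
3. Add a sensitivity analysis that excludes non-cases with no post-baseline CASE questionnaire. This should not become a condition of entry to the primary analysis: it would condition on questionnaire return, which may itself be related to exposure, and would drop cases known only from records. The article's Introduction notes that young people are often reluctant to disclose self-harm. It also notes that studies based on hospital presentations "only reflect those cases of self-harm that are brought to medical attention". Neither source should therefore be discarded from the main result.

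The cost is a few lines of analysis wording, a slightly narrower pool of non-cases and extra model runs. No new data are needed. The self-report-only run gives up some power (74% against 77-79% in the scenario above), which is acceptable for a supporting analysis.
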